## Abstract

**Background:**

Oral anticoagulants (OACs) are commonly prescribed, have well-documented benefits for important clinical outcomes but have serious harms as well. Rates of OAC-related adverse events including thromboembolic and hemorrhagic events are especially high shortly after hospital discharge. Expert OAC management involving virtual care is a research priority given its potential to reach remote communities in a more feasible, timely, and less costly way than in-person care. Our objective is to test whether a focused, expert medication management intervention using a mix of in-person consultation and virtual care follow-up, is feasible and effective in preventing anticoagulation-related adverse events, for patients transitioning from hospital to home.

**Methods and analysis:**

A randomized, parallel, multicenter design enrolling consenting adult patients or the caregivers of cognitively impaired patients about to be discharged from medical wards with a discharge prescription for an OAC. The interdisciplinary multimodal intervention is led by a clinical pharmacologist and includes a detailed discharge medication reconciliation and management plan focused on oral anticoagulants at hospital discharge; a circle of care handover and coordination with patient, hospital team and community providers; and early post-discharge follow-up virtual medication check-up visits at 24 h, 1 week, and 1 month. The control group will receive usual care plus encouragement to use the Thrombosis Canada website.

The primary feasibility outcomes include recruitment rate, participant retention rates, trial resources management, and the secondary clinical outcomes include adverse anticoagulant safety events composite (AASE), coordination and continuity of care, medication-related problems, quality of life, and healthcare resource utilization. Follow-up is 3 months.

**Discussion:**

This pilot RCT tests whether there is sufficient feasibility and merit in coordinating oral anticoagulant care early post-hospital discharge to warrant a full sized RCT.

**Trial registration:**

NCT02777047.

**Supplementary Information:**

The online version contains supplementary material available at 10.1186/s40814-022-01130-z.

## Strengths and limitations of this study

There is a lack of high-quality evidence on hospital discharge strategies which reduce oral anticoagulant (OAC)-related adverse events.Our methods build on our prior research showing that early post-hospital discharge is a high-risk period for adverse events for patients, that coordination of OAC management peri-hospital discharge is hypothesized to reduce events, and that virtual care may be more cost-effective than in person care.This pragmatic pilot randomized trial combines expert multidisciplinary medication management led by Clinical Pharmacology at hospital discharge with virtual care follow-up.Our feasibility outcomes introduce the concept of research resource utilization and management, expressed as cost per patient completing the trial, as a key outcome.

## Introduction

### Background and rationale

Institute for Safe Medication Practices (ISMP) data suggest that approximately 300,000 Canadians suffer serious, disabling, or fatal medication-related harm annually [1, 2]. Anticoagulants are the most common cause of medication-related serious harm, in terms of emergency department visits, hospitalizations, and fatalities [3, 4]. Transitions in care have been identified as a particularly high-risk period for adverse events [5]. Each adverse drug event requiring a hospital visit approximately doubles the cost of care in the subsequent 6 months [1]. Indeed, our previous study of thromboembolic and hemorrhagic events after hospital discharge for patients taking oral anticoagulants (OACs) found rates to be approximately 2 to 3 times higher in the first month compared to later [6]. Root cause analyses and patient safety inquiries cite problems with recognition of individual risk factors for benefit versus harm, drug interactions and contraindications, dosing adjustments over time and around procedures, drug monitoring and reversal strategies, and with communications and poor adherence by patients [7–9]. Furthermore, the direct oral anticoagulants, each with different dosage regimens based on indication and no widely available test to measure the anticoagulant effect, have increased opportunities for medication errors, while greatly increasing drug costs [2, 10, 11].

Anticoagulants are a high priority drug family for improved medication management because of (a) established benefits to reduce the risk for stroke due to atrial fibrillation by approximately 70%, the risk for recurrent venous thromboembolism by more than 90%, and the risk of death by approximately 25%; (b) widespread utilization with more than 12% of people >85 years of age taking OACs and more than 7 million prescriptions dispensed annually in Canada; and (c) ongoing under-prescribing of OACs for eligible patients, over-prescribing of reduced doses off-label, and use of inferior treatments such as aspirin [12–15].

Although there are several well-developed anticoagulation management guidelines with detailed, evidence-informed recommendations, it is difficult for physicians and other health care providers to keep up with evolving evidence, and many patient situations lack high-quality evidence to support a specific approach [16–18]. Thrombosis Canada provides updated, user-friendly succinct clinical guidance for physicians and patients with point-of-care decision support tools; however, the value of supplemental patient education and patient decision aids to improve outcomes remains unproven [19].

Optimal medication safety requires not only best practices based on clinical evidence but also impeccable application and uptake. The latter requires coordination, communication with and education of all key providers, caregivers, and the patient, as well as frequent monitoring, handovers, and constant quality improvement [20–22]. All of these may be most efficiently provided on a large scale across large regions by telehealth or virtual visits [23–25]. However, the effectiveness and cost-effectiveness of telehealth or online interventions for medication management remain uncertain [26, 27]. In addition, methods of coordination and communication of care, including in anticoagulant management programs or clinics vary, although toolkits exist for content guidance [28–30]. Significantly, coordination interventions have rarely involved clinical pharmacologists—medical specialists with expertise in medication management and the ability to diagnose, prescribe, and change prescriptions.

We hypothesize that expert coordination and management of OAC therapy combined with frequent virtual visits by a pharmacist and clinical pharmacologist in the early post-hospital discharge period, plus regular communication with the patient’s circle of care, could decrease adverse anticoagulant-related events and associated healthcare resource utilization while improving patient’s health-related quality of life compared to usual care.

### Objectives

The aim of this pilot randomized controlled trial (RCT) is to test whether high-quality, easily scalable, expert multidisciplinary medication management, and care coordination at hospital discharge and during short-term post-discharge virtual visits are feasible (primary) and can improve oral anticoagulant-related adverse event (thrombotic events, bleeds, and deaths) rates, medication problems, quality-of-life, cost-effectiveness, and satisfaction with care (secondary) during a high-risk transition in care period.

## Methods and analysis

### Trial design and setting

The protocol was developed according to the SPIRIT and TIDieR guidelines [31, 32]. This pragmatic pilot RCT is designed as a 2-arm, parallel, blinded assessment, variable block randomized trial with individual level randomization and outcomes of feasibility and clinical outcomes, during 3 months of follow-up.

Participating sites include 6 hospitals in Southwest Ontario—3 academic teaching hospitals and 3 community hospitals. The trial was originally scheduled to begin in late 2019 but was delayed initially by staff shortages, then by COVID-19 restrictions on hospital-based research [33].

### Eligibility criteria

Inclusion criteria include (a) adult patients within a day of their hospital discharge from internal medicine services with a discharge prescription for an OAC intended to be taken for at least 4 weeks (including both incident and prevalent users), (b) discharge is to home or to a congregant setting such as retirement home where the patient manages their own medications, (c) English-speaking, and (d) capable of providing informed consent. To ensure that we can ethically recruit vulnerable participants including those cognitively impaired, the ability to consent will be measured by the COACHeD Capacity to Consent test, requiring a score of 14 or more (Additional file 3) [34]. If the patient does not pass, a close caregiver (defined as a family member in daily contact with the patient and involved in their medication supervision) will be invited to provide consent on the patient’s behalf by signing a caregiver consent form.

Patients will be excluded if they are less than 18 years of age and have an expected lifespan of less than 3 months and will be discharged to long-term care or other institution where medications are controlled by staff or decline informed consent.

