### Outcomes

Study outcomes, their measurement methods, timing, and analysis are presented in detail in Table 1 and Table 2 and include the following:Primary outcomes, which are study feasibility outcomes, include recruitment and retention rates, and estimated resources required per patient to complete the main trial. Feasibility will be achieved if we can recruit at least 30% of those eligible, retain 90% of those recruited, and spend no more than $1500 per patient running the trial. Secondary feasibility outcomes include barriers and facilitators to success of the primary outcomes, in terms of process and management issues. These will be used to determine whether a large definitive research study is likely to be feasible, taking into account the practical aspects of managing and funding the project [41, 42].Secondary clinical outcomes include the following:The Adverse Anticoagulant Safety Events composite (AASE) which is any of thromboembolic events or clinically relevant bleeding or death. Thromboembolic events include objectively verified ischemic stroke, systemic embolism, pulmonary embolism, or DVT. Clinically relevant bleeds in this study is defined as bleeding that causes death, hospitalization, or emergency department visits.Coordination and Continuity of Care: Adapted from Health Quality Ontario’s draft guidance and a Rand instrument, the Coordination and Continuity of Care Questionnaire is designed to measure the quality of the transitional and follow-up care [5, 43, 44].Patient Quality of Life: The EQ-5D-5L is the 5-level classification system of the EQ-5D, a measure of health status from the EuroQol group [45]. Using EQ-5D-5L, respondents are asked a short series of questions about mobility, self-care, usual activities, pain discomfort, and anxiety/depression, as well as a summary visual analogue scale. This scale, which provides utility measurements, has been well validated for the Canadian population [45–47].Patient Knowledge of OAC Management: Insufficient patient knowledge about OAC may predict poor medication adherence and inadequate anticoagulation control [48]. The COACHeD OAC Knowledge Questionnaire tests knowledge of the therapeutic objective, process of use, safety, and maintenance of the medications [44].Satisfaction with Care: Satisfaction reported by patients and by key health professionals is one of the recommended outcomes to report in medical research, as it may influence adherence [49, 50]. This outcome will be assessed by the Patient/Caregiver Study Satisfaction Survey and by the Provider Study Satisfaction Survey [44].Medication Problems: We will be assessing problems with appropriateness, with medication errors characterized using the National Coordinating Council for Medication Error Reporting and Prevention (NCC-MERP) scale and with medication adherence and attitudes as measured by COMPETE Medication Problems Questionnaire [51, 52].Resource utilization: This is a key outcome to determine cost-effectiveness and cost-utility which then determines whether health care systems might pay for this type of care [53, 54]. We will be measuring all types of health care utilization by patients [43, 46, 54].

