**A. Feasibility outcomes**					
Primary feasibility outcomes	Participant recruitment rates	Continuous (%)	≥ 30% of those eligible will be considered success	Percentage recruited and rate of recruitment (of those screened, of those eligible, and of those approached). Percentage of those recruited (signed informed consent) who complete the end of study assessment at 3 months.	Count of percentages and rates over time
	Participant retention rate	Continuous (%)	≥ 90% is considered success		
	Study resource utilization	Continuous ($CND)	< $1500 per patient recruited and completing the study	Study costs per patient recruited	Cost of personnel, supplies, travel, etc., to run the study/# patients recruited
Secondary feasibility outcomes	Process assessments Management assessments Scientific assessments	Mix of continuous, categorical, and qualitative data	Implementation is successful and feasible, questionnaires are acceptable, and data gathered are reliable and valid	Detailed questions in feasibility assessment	Descriptive
**B. Clinical outcomes**	**Hypothesis**				
Primary clinical outcome	Adverse anticoagulant safety event composite (AASE)	Continuous (%)	Intervention group will have fewer AASE compared to the control group	Count of AASE at the end of the study (3 months). Rates will be expressed as mean rate per patient-year by research assistant.	Chi-square test
Secondary clinical outcomes	Coordination and continuity of care	Continuous	Intervention will have higher ratings than control	Coordination and continuity of care questionnaire partially administered post-discharge and finalized at study end (3 months) by telephone.	*T* tests
	Patient quality of life	Continuous	Intervention will improve more than control	EQ5D-5L—difference in mean change scores at the end of the study.	*T* tests
	OAC management knowledge - patient	Continuous	Intervention will have higher scores than control	OAC knowledge questionnaire	*T* tests
	Satisfaction with care (providers & patients)	Continuous	Intervention will have higher scores than control	Satisfaction questionnaires	Descriptive analysis
	Medication Problems	Continuous	Intervention will have fewer medication problems than control	Composite of OAC-APEQ, COMPETE adherence, and medication error scores	*T* tests
	Cost-effectiveness	Continuous	Intervention will be cost-effective compared to control using a threshold of $50,000 per QALY.	Cost per AASE avoided and cost per quality-adjusted life-years (QALYs)	Economic analysis

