	Individual Clinical Events: a) Bleeding events (clinically relevant), b) Thromboembolic events (all); c) Deaths; d) Hospitalizations or ED visits	Continuous	Intervention will have lower event rates than control	Event rate counts from end-study interviews	*T* tests

**Table 2 Tab2:** COACHeD schedule of events

Assessment	Enrolment		Study in-progress			Study end
	Baseline	Hospital discharge	24h	1Week	1 month	3 months
Eligibility screen	A					
COACHeD Brief Assessment of Capacity to Consent	B					
Informed consent	1/C					
Coordination Continuity of Care Questionnaire (CCCQ)	I/C					I/C
EQ-5D-5L v10-Canada	1/C					I/C
OAC knowledge test	I/C					I/C
Randomization and allocation	I/C					
Discharge medication reconciliation and management, circle of care communication and coordination		I				
Virtual Visit Call #1			I			
Virtual Visit Call #2				I		
Virtual Visit Call #3					I	
Adverse anticoagulant safety events (AASE)						I/C
AASE individual components						I/C
Patient/Caregiver Satisfaction Questionnaire						I/C
Provider Satisfaction Questionnaire						I/C
Health Resource Utilization Questionnaire						I/C
Medication-related problems						I/C

*A*, all potentially eligible patients; *B*, all eligible and interested patients; *I*, intervention patient; *C*, control patient; *I/C*, both groups

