### Statistical analyses

The reporting of the results of this trial will follow the CONSORT extension to pilot trials [41]. We will use descriptive statistics for presentation of baseline variables and adequacy of follow-up. Feasibility analysis including recruitment rate (≥30% is considered success), participant retention rate (≥90% to end of study is considered success), study resource utilization required (CAD $1500 per patient recruited and completing the study is considered a threshold), management assessment, and scientific assessment will be descriptive.

Analysis will use intention-to-treat methods with censoring only if the patient dies or drops out of the study with refusal of negotiated further assessments. A sensitivity analysis of the subgroup of patients who received all 3 planned follow-up intervention calls and completed the end-study data collection (per protocol analysis) will be carried out. Research staff and statisticians will review outcome data and analysis blinded to group identification.

The primary clinical endpoint will be the incidence of adjudicated AASE during the follow-up period, using proportions, and chi-square testing. Secondary endpoint analyses of the coordination and continuity of care, patient quality of life, OAC management knowledge satisfaction with care (providers & patients), and resource utilization will be analyzed using *t* tests. The incidence of the adjudicated individual clinical events (clinically relevant bleeding events, thromboembolic events, all-cause hospitalizations, and emergency department visits) will be analyzed using the methods described above for AASE. Public unit costs from Ontario will be used to cost healthcare resource utilization collected as part of the trial. Using an area under the curve approach, quality-adjusted life years (QALYs) will be determined by weighting the EQ-5D-5L health utility scores by time spent in health state. Costs and outcomes (i.e., QALYs, AASE) between the interventions will be compared from a public payer perspective. Given the short follow-up, a low risk of the trial and pilot design, no interim analysis or imputation for missing data is planned. All analyses will be performed using SAS V9.4 software (SAS Institute Inc., Cary, NC, USA).

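### Refusing consent is an exclusion criterion while the 30% recruitment threshold applies to those eligible, so the first primary feasibility criterion has two incompatible denominators

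*Protocol article*

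**What the plan says.** The Eligibility criteria section ends its list of exclusions with discharge to long-term care or an "other institution where medications are controlled by staff or decline informed consent". Refusal is thus listed as an exclusion.

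The Outcomes section makes recruitment the first of three primary feasibility conditions: "Feasibility will be achieved if we can recruit at least 30% of those eligible". Table 1 repeats it as "≥ 30% of those eligible will be considered success". The Statistical analyses section gives the same threshold with no denominator: "recruitment rate (≥30% is considered success".

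Elsewhere eligibility comes before consent:
- Table 1 lists three separate bases for reporting: "Percentage recruited and rate of recruitment (of those screened, of those eligible, and of those approached".
- The Table 2 legend gives the capacity test to "all eligible and interested patients", so interest is something added to eligibility.
- The Allocation section names satisfying the criteria at screening and completing consent as two conditions for enrolment.

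Two further wordings affect who counts. Inclusion (d) requires the patient to be capable of consenting, yet for a patient who fails the capacity test "a close caregiver (defined as a family member in daily contact with the patient and involved in their medication supervision) will be invited" to consent instead. The other exclusions are chained by the word *and*: "less than 18 years of age and have an expected lifespan of less than 3 months and will be discharged".

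**The concern.** The recruitment criterion is there to warn that a definitive trial could not recruit, and refusal is a main reason why it might not. If refusal makes a patient ineligible, the rate that carries the threshold does not respond to refusal at all. If eligibility is settled before consent, every refusal lowers it. The article supports both readings and nowhere says that decliners count as eligible.

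The Outcomes section says the feasibility results will be used to judge whether a large definitive study is likely to be feasible. If the denominator is left open until the rates are calculated, it could be chosen with the results in view.

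**Working it through.** **The plan's own figure.** Sample size estimation states that 59 participants allow a problem of 5% probability to be identified with 95% confidence. n = ln(1 − 0.95)/ln(1 − 0.05) = 58.40, rounded up to 59. Check: 1 − 0.95^59 = 0.9515 and 1 − 0.95^58 = 0.9490. The figure reproduces and is unaffected by this point. The 30% threshold has no stated derivation to check.

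**Inputs.** R = 59 recruited (Sample size estimation). Threshold 30% (Outcomes, Table 1). D = decliners, and M = eligible patients who did not decline but were missed or not approached. The documents give neither D nor M; the ranges used here, 0 to 300 and 0 to 200, are assumptions.

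**Formulas.**
- Decliners counted as eligible: R/(R + D + M).
- Decliners removed, as the exclusion is written: R/(R + M).

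**Break point.** 59/0.30 = 196.7, so the criterion is met with a denominator of up to 196 (59/196 = 30.1%) and fails at 197 (59/197 = 29.9%). Since 197 − 59 = 138, it fails when D + M reaches 138 on the first reading, and only when M alone reaches 138 on the second.

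| D | M | Decliners counted | Decliners removed |
|---|---|---|---|
| 60 | 0 | 49.6% | 100% |
| 137 | 0 | 30.1% | 100% |
| 138 | 0 | 29.9% | 100% |
| 200 | 0 | 22.8% | 100% |
| 300 | 0 | 16.4% | 100% |
| 200 | 30 | 20.4% | 66.3% |
| 60 | 100 | 26.9% | 37.1% |
| 0 | 138 | 29.9% | 29.9% |
| 0 | 200 | 22.8% | 22.8% |

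The readings give opposite verdicts whenever M is at most 137 and D + M is at least 138. With M = 0 that needs 138 decliners; with M = 30 it needs 138 − 30 = 108; with M = 100 it needs 38.

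**Recruitment quota instead of 59.** Six sites with 10 to 12 patients each (Trial design and setting; Recruitment methods) give 60 to 72. The largest passing denominators are 60/0.30 = 200 and 72/0.30 = 240, so with M = 0 the disagreement starts at 141 and 169 decliners. The pattern is the same.

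**The case against.** **A reader might infer that the criterion cannot fail, or that the rate is near 100% whatever the uptake.** The documents do not support that. Eligible patients who are missed or not approached stay in the denominator on either reading, and Recruitment methods describes discharge as rushed and its timing as unstable, so misses are a real possibility. At 138 missed per 59 recruited the criterion fails even with every decliner removed. What holds is narrower: refusals alone cannot make it fail.

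**The intended meaning is probably the pre-consent one.** Tables 1 and 2 and Allocation all point that way. This stands as evidence of which wording is the slip, but it does not remove the conflict: the section that defines eligibility says the opposite.

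**Heavy refusal would be visible anyway.** Table 1 also reports recruitment as a percentage of those approached. That is correct, and so it would be wrong to say that the trial gives no warning. But only the percentage of those eligible carries the threshold.

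**The exclusion sentence is ambiguous.** If each *and* binds strictly, refusal could attach only to the last item and would not exclude by itself. That parse leaves an almost empty exclusion, because inclusion (a) already requires adults. On the natural reading, as a list of separate exclusions, refusal excludes alone.

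**Counting rules belong in a fuller document.** A missing counting rule would be no finding. The point here is that two statements in the article disagree.

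**Counting missed patients adds a new denominator.** It does not. They meet the criteria, and Table 1 already separates those eligible from those approached.

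**Conclusion.** The point holds as an inconsistent definition of the denominator for the first primary feasibility threshold. With 59 recruited and no eligible patient missed, the two readings disagree from 138 decliners upward; at 200 decliners they give 59/259 = 22.8% (fail) and 59/59 = 100% (pass). These sizes rest on assumed counts of decliners and missed patients. With fewer decliners and few misses both readings pass, and with 138 or more missed both fail.

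Two drafting points are secondary and do not carry the conclusion. First, inclusion (d) taken alone would put caregiver-consented patients in the numerator but outside the denominator. The sentences that follow it, and the abstract's Methods, show that they are meant to be enrolled. Second, the chained *and* taken literally leaves short life expectancy without effect as an exclusion of its own, since the inclusion criteria cover age and discharge setting but not life expectancy. This is most likely a slip. A reader might infer that patients not expected to survive follow-up will be enrolled, but the documents do not show such an intention.

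**What to change.** - Delete refusal of consent from the exclusion criteria.
- State, in Outcomes, Table 1 and Statistical analyses alike, that the 30% denominator is all patients meeting the eligibility criteria other than consent, with decliners and eligible patients missed or not approached counted. Capacity to consent should be treated as part of consent here: Table 2 gives the capacity test only to interested patients, so capacity will not be known for the others.
- Keep the percentages of those screened and of those approached as supporting figures.
- Reconcile inclusion (d) with the caregiver route, so that caregiver-consented patients count in both numerator and denominator.
- List the remaining exclusions as separate criteria, each excluding on its own.

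The cost is eligibility wording and a screening-log definition that records decliners and missed patients. No sample size or comparative analysis changes. The reported recruitment rate may be lower. The definition should be settled before any recruitment rate is calculated.
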